### Other outcomes

#### Oxidative stress-associated suppression of endothelial function

Tonic suppression of endothelial function by oxidative stress will be assessed by measuring the improvement in FMD_BA_ from baseline (saline control) in response to acute (intravenous) infusion of supraphysiological concentrations of vitamin C, a potent antioxidant that scavenges reactive oxygen species (ROS) (Eskurza et al., 2004; Walker et al., 2012; Jablonski et al., 2013). A bolus dose of 0.06 g vitamin C/kg fat-free mass dissolved in 100 ml of saline will be infused intravenously at a rate of 5 ml/min for 20 min, followed immediately by a “drip-infusion” of 0.02 g/kg fat-free mass dissolved in 30 ml of saline infused at a rate of 0.5 ml/min. FMD_BA_ will be performed as described above at the end of the 20-min bolus during the “drip infusion,” when peak levels of vitamin C occur (Eskurza et al., 2004).

#### Endothelial cell protein abundance

Endothelial cell markers of oxidative modification of proteins (nitrotyrosine abundance), pro-oxidant signaling (NADPH oxidase subunit p47^phox^) and antioxidant defenses (manganese superoxide dismutase) will be assessed using methods established in our laboratory (Donato et al., 2008; Pierce et al., 2011a; Jablonski et al., 2011). Endothelial cells will be collected from an antecubital vein by a trained nurse using 2 sterile 0.025-inch J-wires briefly advanced through an intravenous catheter. Cells will be recovered by centrifugation, fixed with formaldehyde, and slides will be prepared and frozen for later analysis.

Slides will be stained for the primary antibody of interest and a complementary fluorescent secondary Alexafluor 647 antibody (Invitrogen). Slides will also be stained for positive identification of endothelial phenotype and with DAPI for nuclear integrity. Images will be captured digitally and analyzed using Image J software (NIH). Values will be reported as ratios of subject endothelial cell protein expression to human umbilical vein endothelial cell (HUVEC) control protein expression to remove the possible confound of differences in intensity of staining between sessions. Importantly, we have shown that endothelial cells sampled from peripheral veins provides the same information as arterial sampling without the need for invasive brachial artery catheterization (Silver et al., 2010).

#### Endothelial cell nitric oxide and reactive oxygen species production with serum exposure

In order to determine the role of circulating factors in modulating endothelial cell function, NO and ROS production will be measured in HUVECs treated with serum obtained from subjects before versus after 3 months of high-resistance IMST or aerobic exercise as previously described (Craighead et al., 2021b). HUVECs (PromoCell; used after 2–4 passages) will be plated in 96-well culture plates and incubated with basal media supplemented with 10% subject serum under standard conditions (37°C, 5% CO_2_) for 24 h. Following incubation, cells will be co-incubated with fluorescent dye mixture (DAR-4M AM and CellROX Deep Red). Fluorescent imaging of cytoplasmic DAR-4M AM before and 5 min after addition of 100 µM acetylcholine will quantify the capacity of HUVECs to generate NO while basal CellROX fluorescent intensity will quantify intracellular ROS levels. Analysis will be done with Celleste (Invitrogen) and data expressed as a fold change from NO or ROS production with baseline (pre-intervention) serum exposure.

To assess the specific circulating factors involved in mediating changes in endothelial cell function, HUVECs also will be cultured with plasma metabolites that change significantly with IMST or aerobic exercise training (identification of these metabolites described below in Targeted Plasma Metabolomics). The HUVECs will be cultured as described above with and without identified metabolites administered at estimated physiological concentrations observed after IMST or aerobic exercise, and NO and ROS production will be measured.

#### Targeted plasma metabolomics

We will use targeted plasma metabolomics to identify circulating factors contributing to potential changes in endothelial cell NO and ROS production with IMST or aerobic exercise. Subject plasma obtained before and after the IMST and aerobic exercise interventions will be analyzed as described previously (Gehrke et al., 2017). Briefly, plasma samples will be thawed on ice. A 20 µL aliquot of plasma will be diluted with 480 µl of ice-cold methanol/acetonitrile/water (5/3/2). Extractions will be performed as previously described (Nemkov et al., 2015). Supernatants from the extraction will be analyzed with a 5-min C18 gradient on an ultra-high-performance liquid chromatograph (Thermo Fisher Vanquish) coupled with a mass spectrometer (Thermo Fisher Q Exactive). Raw files will be converted to mzXML format (RawConverter, Yates Laboratory, The Scripps Research Institute). Metabolite assignments will be made using Maven (Princeton, NJ).

#### Safety and tolerability

Safety, i.e., risk to the subject, of both treatment arms will be assessed by recording adverse events during the intervention. Tolerability, i.e., the degree to which overt adverse events are tolerated by participants, will be determined based on the number of participants that drop out of the study due to adverse events.

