One such potential intervention is high-resistance inspiratory muscle strength training (IMST), which involves breathing in against resistance through a handheld device (Craighead et al., 2019). In contrast to conventional inspiratory muscle training against low-to-moderate levels of resistance performed for extended durations, high-resistance IMST utilizes a low number of repetitions against a near-maximal resistance, resulting in a daily time commitment of only approximately 5 min, overcoming the critical time-availability barrier (Craighead et al., 2021a). Additionally, by using an affordable, portable device, high-resistance IMST overcomes many common barriers associated with aerobic exercise and holds promise for future public health translation (Craighead et al., 2022). However, the efficacy of high-resistance IMST for inducing cardiovascular health benefits, particularly in estrogen-deficient postmenopausal women, needs to be firmly established.

We recently completed a pilot study in midlife/older men and women (aged 50–79 years) with above-normal initial SBP comparing 6 weeks of high-resistance IMST (30 breaths/day, 6 days/week, 75% maximal inspiratory pressure [PI_MAX_]) to low-resistance (15% PI_MAX_) sham control training. IMST was safe (no serious adverse events), tolerable (no dropouts due to adverse events) and promoted adherence (94% of prescribed training sessions performed) (Craighead et al., 2021b).

In this pilot trial, IMST also induced clinically meaningful improvements in cardiovascular function. Casual SBP was reduced by 9 mmHg and this reduction was ∼75% sustained 6 weeks after completing the last IMST training session; casual DBP also was reduced by 2 mmHg. Twenty-four-hour SBP, a CVD risk factor independent of casual SBP (Clement et al., 2003; Dolan et al., 2005), decreased by 4 mmHg. Brachial artery flow-mediated dilation (FMD_BA_), a measure of endothelial function, was increased by approximately 45%. Improvements in cardiovascular function were associated with reductions in oxidative stress and increased NO bioavailability (Craighead et al., 2021b).

Although establishing the sex-specific effects of IMST was not a primary objective of our trial due to a limited sample size, our initial results suggested IMST was at least equally as effective for lowering SBP and improving endothelial function in estrogen-deficient postmenopausal women as in age-matched men (Craighead et al., 2021b).

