#### Intervention abstention and follow-up testing

Once all end-intervention data have been collected, participants will return their training device (POWERBreathe K3 or Polar OH1 heart rate monitor) to the study staff and be instructed to halt their assigned intervention for a 6-week free-living period. During this 6-week period, participants will be asked not to make any lifestyle changes (outside of abstention from the study intervention). Participants will return to the laboratory 6 weeks later to perform follow-up testing for casual BP, 24-h BP, and FMD_BA_ (Visits 15 and 16, Figure 2) to determine the potential persistent effects of high-resistance IMST or moderate-intensity aerobic exercise on BP and vascular function (study primary and secondary outcomes).

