#### Adverse events

Participants will be instructed to inform members of the study team of any adverse events they experience while enrolled in the study. Mild and moderate adverse events will be regularly reported to the University of Colorado Boulder Institutional Review Board (IRB), National Institutes of Health, and the study data safety monitoring board. Serious adverse events will be reported to the study medical director within 24 h of the study team’s awareness of the adverse event and to the University of Colorado Boulder IRB within 5 days. An unanticipated adverse event which meets the University of Colorado Boulder IRB definition of an unanticipated problem (i.e., any unanticipated and undesirable effect arising from participation in research that results in an increased risk of harm or injury to a subject, or which suggests the possibility of increased risks to other subjects) will be reported to the University of Colorado Boulder IRB using the corresponding form within 5 days of occurrence.

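### The safety outcome stops when training stops, although both arms are followed for efficacy for a further 6 weeks

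*Protocol article*

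**What the plan says.** Four statements in the protocol article bear on this point.

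- **Safety outcome** (Other outcomes, Safety and tolerability): the safety of both arms "will be assessed by recording adverse events during the intervention".
- **Tolerability outcome** (same paragraph): it "will be determined based on the number of participants that drop out of the study due to adverse events".
- **Participant reporting** (Adverse events): "Participants will be instructed to inform members of the study team of any adverse events they experience while enrolled in the study". These reports go to the IRB, and mild and moderate events also go to the funder and the data safety monitoring board.
- **Abstention period** (Intervention abstention and follow-up testing): after end-intervention testing, participants will "be instructed to halt their assigned intervention for a 6-week free-living period". They then return for casual BP, 24-h BP and FMD at Visits 15 and 16.

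The Statistical design, power, and analysis plan section puts the 6-week follow-up data into the mixed model and states that safety and tolerability will be described qualitatively. The Expected results section anticipates fewer intervention-related adverse events and fewer dropouts due to adverse events with IMST, and reads this as greater safety and tolerability. The Discussion and the Novelty and innovation section also promise conclusions on safety, the latter as a direct comparison of the two interventions.

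**The concern.** The article treats the 6 weeks after training as part of the trial for efficacy but not for the safety outcome. Casual SBP, 24-h SBP and FMD are measured at the end of that period, and the authors expect the benefit of IMST to persist through it. An adverse event in the same weeks would be reported by the participant but would not count in the outcome used to compare the arms. Benefit and harm would then be described over different times.

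The Safety and tolerability paragraph also uses two time frames. A woman who leaves the study in week 3 of abstention because of an adverse event counts as a tolerability failure, yet her event falls outside safety. A reader of the results could find a dropout due to an adverse event with no matching event in the safety outcome.

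**Working it through.** The plan gives no figure for the length or yield of the safety window, so there is none to reproduce. The sample size (36 per group, 45 enrolled per group) does not enter. The check compares time windows and then sizes the gap.

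**1. Windows side by side**

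| Item | Section | Window |
|---|---|---|
| Safety outcome | Safety and tolerability | During the intervention |
| Tolerability outcome | Safety and tolerability | Dropout from the study |
| Event reporting | Adverse events | While enrolled |
| BP and FMD | Outcomes; Intervention abstention and follow-up testing; Statistical design, power, and analysis plan | Baseline, end of intervention, 6 weeks after stopping |

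Only the safety outcome ends with the intervention. No section extends it.

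**2. Length of the excluded period**

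Inputs: training 3 months (Intervention), taken as 13 weeks; end-intervention testing up to 10 days with training continued (End-intervention assessments), which is 10/7 = 1.4 weeks; abstention 6 weeks (Intervention abstention and follow-up testing). The article gives no duration for the follow-up tests themselves, so none is added.

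- Without end-testing: 13 + 6 = 19 weeks; 6/19 = 32%.
- With the full 10 days of end-testing: 13 + 1.4 + 6 = 20.4 weeks; 6/20.4 = 29%.
- If 3 months is taken as 12 weeks, without end-testing: 6/18 = 33%.

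So about 30% of the time after randomisation lies outside the safety outcome, in each arm.

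**3. How many events that could be**

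The documents give no adverse event rate for the abstention period. As an assumption only, let the probability of an event in those 6 weeks be r per participant, with the planned 36 completers per arm. The expected number of participants with an event is 36r, and the chance of at least one is 1 − (1 − r)^36.

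| r (assumed) | Expected per arm | Chance of at least one |
|---|---|---|
| 0.5% | 0.18 | 17% |
| 1% | 0.36 | 30% |
| 2% | 0.72 | 52% |
| 5% | 1.8 | 84% |

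This range is too wide to say whether the reported comparison would change. It shows only that a few events could fall outside the outcome, and that none might.

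**The case against.** The strongest reply is that the two sections do different jobs. Safety and tolerability defines a study outcome; Adverse events sets participant reporting and notification. An on-treatment outcome inside a wider reporting window is a common design and not in itself a contradiction. That stands, and it rules out one tempting inference: that events in the abstention period are lost or escape oversight. They are reported, and the board reviews safety data twice a year. BP is also measured at the end of abstention, so BP at that point is observed.

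It is also fair to say that the expected advantage concerns intervention-related events, which suits an on-treatment window, and that a condensed article leaves flags and tabulation rules to a fuller document. But the window here is stated, not left open, and it differs from the one used for tolerability in the same paragraph and from the one used for efficacy.

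Three further readings are tempting and are not supported.

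- **That exposure continues after training.** The article reports a pilot SBP reduction of 9 mmHg that was about 75% "sustained 6 weeks after completing the last IMST training session". That is a persisting effect, not persisting exposure. It comes from a mixed-sex pilot of 6 weeks of IMST and says nothing about aerobic exercise. No section describes a risk of low or rebounding BP during abstention.
- **That the Adverse events section wrongly mixes events before and after randomisation.** It neither tabulates by arm nor defines a comparison, and oversight should include events from screening and baseline procedures.
- **That about 30% of adverse events would be missed.** The figure is calendar time.

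**Conclusion.** The point holds in a limited form. As written, the between-arm safety outcome covers the training period and leaves out the 6-week abstention period in both arms, about 29% to 32% of the time after randomisation. Efficacy and tolerability are carried through that period, and conclusions on comparative safety are planned. The result rests on the plain reading of "will be assessed by recording adverse events during the intervention" and on taking 3 months as 13 weeks, with or without 10 days of end-testing. The number of events affected cannot be derived from the documents.

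Severity is low. Safety is described qualitatively, event capture and oversight are intact, and no test, power figure or efficacy conclusion depends on the window. The cost of leaving it is an avoidable mismatch between the periods over which benefit and harm are reported.

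**What to change.** Change the sentence under Safety and tolerability so that, in both arms, the safety outcome counts all adverse events from randomisation to the last follow-up visit (Visit 16), reported separately for the training and abstention periods. This keeps the on-treatment count visible and adds the period over which persistence is claimed. List events before randomisation apart from the arms, since they cannot belong to either.

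Leave the reporting window in the Adverse events section as it is. Narrowing it to start at randomisation would remove screening and baseline events from oversight reporting.

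The cost is one sentence of wording, a period flag on the adverse event form and slightly more tabulation. Visits 15 and 16 and the reporting duty already exist.

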#### Intervention

##### High-resistance inspiratory muscle strength training

Participants in the high-resistance IMST group will train using the POWERBreathe K3 tapered-resistance inspiratory training device. Individual training sessions will entail performing 30 inspiratory maneuvers, consisting of 5 sets of 6 inspirations with a 1-min rest between sets. Training sessions will be performed 6 days per week for 3 months. Subjects will continue to train during the end-intervention testing period (described below) to maintain the training effect.

Inspiratory resistance on the POWERBreathe K3 will be set to 55% of each individual’s PI_MAX_ during week 1 of training, 65% of PI_MAX_ during weeks 2 and 3 of training, and then at 75% of PI_MAX_ throughout the remainder of the intervention. PI_MAX_ will be reassessed during supervised training sessions and check-in visits and the absolute training intensity adjusted to account for improvements in inspiratory muscle function throughout the intervention.

The first IMST training session will be supervised in the laboratory by an unblinded research assistant to train the participant on proper IMST technique (Visit 6, Figure 2). A second IMST training session will be supervised 1 week later to ensure maintenance of the proper technique (Visit 7, Figure 2). All other training sessions will be performed unsupervised, but with training documented by the internal storage of the POWERBreathe K3 training device.

PI_MAX_ will be assessed at baseline, during check-in visits (Visits 8-11, Figure 2) and during end-intervention testing to maintain an appropriate training stimulus and document changes in inspiratory muscle strength. To calculate PI_MAX_ subjects will perform a series of maximal inspiratory efforts against a near-infinite resistance using the POWERBreathe KH2 device and associated Breathlink software. The average of the 3 largest pressures generated will be calculated as PI_MAX_ (Kellerman et al., 2000; Vranish and Bailey, 2015). PI_MAX_ also will be measured at baseline and end-intervention in the moderate-intensity aerobic exercise group to allow for comparisons between groups.

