The same linear mixed effects model will be used to evaluate the intervention effect on our mechanistic outcomes at baseline and end-intervention. In addition, the association between the change in FMD_BA_ and changes in mechanistic probes will be assessed and linear regression model analysis used to adjust for potential confounders. Finally, mediation analysis will be used to provide evidence for a potential causal influence of our mechanistic probes for contributing to changes in FMD_BA_ with IMST or aerobic exercise (Mascha et al., 2013; Valente et al., 2017).

Adherence will be calculated as the percentage of prescribed training sessions performed appropriately and compared between groups with an unpaired t-test. Safety and tolerability will be described qualitatively.

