**FIGURE 3 F3:**
[figure not shown]
Expected Results. Expected results for **(A)** casual systolic blood pressure (SBP; primary outcome) and 24-h SBP (secondary outcome); and for **(B)** endothelial function measured by brachial artery flow-mediated dilation (FMD_BA_; secondary outcome) in the high-resistance inspiratory muscle strength training (IMST) and moderate-intensity aerobic exercise groups across the intervention. Dashed line represents expected FMD_BA_ with supratherapeutic infusion of the potent antioxidant, vitamin C, in both subject groups.

We also expect a greater improvement in FMD_BA_ following high-resistance IMST compared to aerobic exercise training, and that the improvement in FMD_BA_ following IMST will be at least partially sustained 6 weeks later (Figure 3B).

At end-intervention, we anticipate that high-resistance IMST will reduce or abolish the acute increase in FMD_BA_ observed after systemic infusion of vitamin C at baseline, but that aerobic exercise training will have no effect (Figure 3B). We expect that in biopsied endothelial cells, high-resistance IMST will decrease nitrotyrosine (marker of oxidative stress), decrease the expression of the oxidant enzyme NADPH oxidase, and increase expression of the antioxidant enzyme MnSOD to a greater extent than aerobic exercise training. We also expect endothelial cells cultured with subject serum obtained after (vs. before) IMST will increase NO and decrease ROS production more than serum obtained after (vs. before) aerobic exercise training. We also expect to identify changes in circulating metabolites with IMST that more greatly modulate endothelial cell NO and ROS production than aerobic exercise training does.

In addition, we expect to observe higher rates of adherence to the high-resistance IMST intervention compared to aerobic exercise training. Finally, we expect to observe fewer intervention-related adverse events and dropouts due to adverse events in the IMST group, suggesting greater safety and tolerability of IMST compared to aerobic exercise.

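### Tolerability counts participants who leave the study because of an adverse event, so a participant who stops or reduces her training for one but stays in the study is scored as tolerating it

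*Protocol article*

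**What the plan says.** The protocol article states as an aim, at the end of Background and rationale, that it will assess how safe and tolerable the two interventions are and how well they are adhered to. The Safety and tolerability section then fixes the measures:

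- Safety "of both treatment arms will be assessed by recording adverse events during the intervention".
- The concept of tolerability is broad: "Tolerability, i.e., the degree to which overt adverse events are tolerated by participants".
- The measure of tolerability is narrower: it "will be determined based on the number of participants that drop out of the study due to adverse events".

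The Adherence section defines adherence as the share of prescribed sessions done at the right duration and intensity, read from the training device or the heart rate monitor. It names no reason for missed sessions. In the IMST arm, after two supervised sessions, "All other training sessions will be performed unsupervised". The aerobic arm follows the same pattern. Both arms have check-in visits (Visits 8-11).

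The statistical section says: "Safety and tolerability will be described qualitatively". Expected results and their interpretation anticipates fewer "dropouts due to adverse events in the IMST group, suggesting greater safety and tolerability of IMST compared to aerobic exercise". The Discussion and its Novelty and innovation part say that the trial will determine whether IMST is tolerable and will compare tolerability directly between the arms.

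**The concern.** The aim concerns the training, but the measure counts exits from the study. These are different events when training is done mostly at home and attendance is separate from it. A participant with an adverse event can cut back or stop training and still attend every visit. She did not tolerate the intervention, but the stated rule counts her as if she did.

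At stake is the between-arm statement on tolerability. The article could report no adverse-event dropouts in an arm, and hence good tolerability, although some participants in it had stopped training because of adverse events. None of the measures as described would bring these cases together.

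**Working it through.** **1. The plan's figures.** No number is attached to the tolerability outcome, so there is none to reproduce. The denominator comes from the statistical section: 36 per group with about 20% dropout gives 36 / (1 − 0.20) = 45 per group, as the article states.

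**2. How much training is out of sight.** The schedule is 6 sessions a week for 3 months. Taking 3 months as 13 weeks (an assumption), 6 × 13 = 78 sessions. Two are supervised, leaving 76, and 76/78 = 97%. Staff also see participants at Visits 8-11, so contact is not limited to the two supervised sessions.

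**3. How each record treats a randomised participant.**

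| Case | Tolerability as defined | Adherence | Adverse event record |
|---|---|---|---|
| Leaves the study because training caused an adverse event | Counted | Sessions missing | Event, if reported |
| Stops or cuts back training because of an adverse event, stays in the study | Not counted | Sessions missing, no reason | Event, if reported; no stated link to the missed sessions |
| Stops or cuts back training for lack of time, stays in the study | Not counted | Sessions missing, no reason | Nothing |
| Leaves because of an adverse event from a test procedure at end-intervention | Counted | Little or no effect | Event, if reported |

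The second and third rows score the same on tolerability and adherence, although only the second is intolerance. An adverse event record could tell them apart if it were linked to the training stop, but the article describes no such link.

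**4. Could the second row occur?** Individual subject stopping criteria covers only leaving the study or being removed from it. It neither describes nor excludes stopping training while staying in follow-up. If prolonged non-training led to removal for non-compliance, the recorded cause might be non-compliance, and the tolerability count takes only exits due to adverse events.

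**5. What a zero count would show.** The pilot had no adverse-event dropouts. If that repeats, an arm shows 0/45. The exact two-sided 95% upper limit is 1 − 0.025^(1/45) = 0.079, or 7.9%. That limit applies to leaving the study because of an adverse event. It does not bound the proportion who stop training because of one.

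**6. Size per case.** Each participant in the second row moves the arm's figure by 1/45 = 2.2 percentage points. The documents give no rate for such cases, so no total can be computed.

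**7. The fourth row.** Baseline testing precedes randomisation, so an exit after a baseline procedure belongs to no arm. Follow-up testing is listed as casual blood pressure, 24-hour blood pressure and flow-mediated dilation only. The vitamin C infusion, J-wire cell collection and maximal treadmill test therefore recur after randomisation only at end-intervention, within 10 days or less, and equally in both arms.

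**The case against.** The strongest reply is that tolerability is one of three linked measures. Adverse events are recorded in both arms, participants are told to report them, and adherence is read from the devices and compared by t-test. A participant who stops training for an adverse event would appear as poor adherence and, if she reports it, as an adverse event. This stands in part: the trial is not blind to her. What is missing is the link between the two records, and without it she is still counted as tolerating the training.

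The definition also matches the pilot's, so changing it could cost comparability. That is fair, and reporting both counts answers it.

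The outcome sits under Other outcomes, is described qualitatively, and the comparative statement is an expectation. This limits the weight of the point but does not remove it, because a tolerability conclusion is still planned on this count. The pilot's 94% of IMST sessions performed also gives no sign of widespread hidden stopping there, although that was over 6 weeks.

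Three stronger readings are not supported:

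- A reader might infer that the measure is biased towards IMST. The documents give no basis for a direction, since participants in either arm could stop training and stay.
- A reader might infer that exits after test procedures seriously contaminate the count. As step 7 shows, the exposure is short and the same in both arms.
- A reader might infer that removals by the investigators for an adverse event fall outside the count. Such a removal reads naturally as an adverse-event dropout, and nothing excludes it.

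**Conclusion.** The point holds for the definition. Tolerability of the training is measured by leaving the study because of an adverse event, so a participant who stops or reduces training for that reason but stays is scored as tolerating it. Adherence as described does not supply the reason. This is a possible misclassification, not a certain one, and its frequency is unknown. It rests on one assumption: that participants who stop training can remain in the study, which the article does not rule out. Each case is worth 2.2 percentage points in an arm of 45.

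The procedure issue is minor. The primary and secondary outcomes and the sample size are unaffected. The change is worth making because the article plans a between-arm conclusion on tolerability and a better measure is available at almost no cost.

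**What to change.** In Safety and tolerability, define tolerability as the number of randomised participants per arm who permanently stop, interrupt or reduce their assigned training because of an adverse event, whether or not they remain in the study. Identify changes in training from the session logs already stored on the POWERBreathe K3 and Polar OH1, and record the reason at Visits 8-11. An unblinded staff member should record it, so that outcome assessors stay blinded.

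Report adverse-event dropouts from the study alongside, for comparison with the pilot, and give the attributed cause of each (training or test procedure). Base the tolerability statement in Expected results on the new count.

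The cost is one case report form item, with no new visit or device. The downside is that the tolerability figure may look less favourable than the pilot's. The change concerns only what is counted; it sets no rule for when anyone should stop training.
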